## Abstract

**Background:**

Problems with sustained attention, impulsivity, and hyperactivity are the most prominent symptoms of attention-deficit hyperactivity disorder (ADHD), but many children with this diagnosis also present with poor organizational skills that are important in relation to school. These problems tend to increase from childhood to adolescence and are often not well managed by medication. Organizational skills training (OST) is a range of behavioral interventions that specifically target organizational skills deficits. Evidence supports the effect of OST on improving organizational skills, inattention, and academic performance in children with ADHD. Because previous clinical trials included mostly children above the age of 8 years, this trial includes children in the age range 6–13 years to expand the knowledge on the effects of OST in younger children. Previous OST research has also shown improvement on inattention in parent ratings; we will investigate if a change in inattention can be confirmed with neurocognitive tests. Finally, little is known about predictors of treatment response in OST.

**Objectives:**

The primary objective is to investigate if OST has positive effects on organizational skills in children with ADHD. The primary outcome measurement is the parent-rated Children’s Organizational Skills Scale (COSS), collected before and at the end of the 10 week intervention. Secondary and exploratory outcomes include inattention ratings, family and school functioning, and cognitive functions measured before the intervention period, immediately after, and at a 6 month follow-up. Additional objectives are to investigate both neurocognitive outcomes and age as predictors of treatment response.

**Methods:**

This is a randomized clinical superiority trial investigating the effect of OST vs a treatment-as-usual (TAU) control group for children with ADHD in the age range of 6–13 years. All participants (*n* = 142) receive TAU. OST is administered in a group format of 10 weekly sessions. Adverse events are monitored by study clinicians during weekly therapy sessions and all assessments. Data analyses will be conducted using mixed linear regression models with random intercepts for patients, adjusted for the stratification variables and the baseline value.

**Perspectives:**

This study will provide important new knowledge and expand on existing research in the field of non-pharmacological treatment of children with ADHD. OST can potentially have a significant impact on the lives of children with ADHD by helping them learn how to cope with their present deficits and to become more independent and self-reliant. It is also important to investigate predictors of treatment response in order to optimize OST.

**Trial registration:**

ClinicalTrials.gov NCT03160378. Registered on May 19, 2017.

**Supplementary Information:**

The online version contains supplementary material available at 10.1186/s13063-021-05499-9.

## Introduction

Attention deficit/hyperactivity deficit disorder (ADHD) is a prevalent neurodevelopmental disorder in childhood [1–3]. An ADHD diagnosis is associated with a number of negative consequences later in life as higher risk of school drop-out [4, 5], a higher susceptibility to other psychiatric disorders, substance abuse, criminality, adverse health events, and premature death [6–11]*.*

ADHD symptoms involve problems with inattention, impulsivity, hyperactivity, and very often a range of cognitive deficits. So far, an ADHD specific cognitive profile has not be identified, as individuals with ADHD present a range of heterogeneous cognitive deficits which are already visible at young age and often stabilize over time [12]. Organizational skills deficits refer to issues such as losing things/forgetfulness, having difficulties with planning or organizing tasks and activities, failing to follow through with instructions, and finishing schoolwork. These four problems with organization and planning ahead are included in the description of ADHD in the Diagnostic and Statistical manual of mental disorders (DSM-5) [13]. Organizational skills deficits are partially an expression of executive dysfunctions that many children with ADHD experience [14–16].

Organizational skills interventions for children and adolescents with ADHD target organizational deficits and include skills for organizing materials (e.g., school notes and handouts) and time (e.g., long-term planning and scheduling) [17]. In ADHD, issues with misplacing materials, procrastination, failure to plan, or organize and prioritize actions all increase in severity over time [18, 19], and often persist into adulthood [20] as the complexity of academic responsibilities increases, while in typically developing individuals such difficulties decrease over time due to brain maturation [21]. Having difficulties with organizational skills often imparts a range of adverse consequences in everyday life including academic underperformance (even in gifted students) and psychosocial, occupational, or economic difficulties [4, 22–26]. In addition, medical treatment for ADHD has limited effect on organizational skills difficulties [27, 28].

Executive functions are the foundations of organizational skills. There is evidence that the development of executive functions starts as early as in pre-school and kindergarten ages and is important for school-readiness and social-emotional development [29]. As these challenges increase with age, it is critical to intervene and address these impairments as early as possible.

Organizational skills interventions include different behavioral techniques like prompting, rehearsal, and contingency management. Parents often play an active part in the treatment by prompting, praising, and rewarding the child with the aim to reinforce specific behaviors and to promote skills generalization. There is a range of different organizational skills interventions, with some interventions focusing strictly on materials organization and others on the process of completing homework and/or parent-child and parent-school relationships surrounding homework [30–33]. Most organizational skills interventions are aiming to teach parents how to monitor, prompt, and reward their child in relation to school related tasks. The ultimate goal is to reduce the frequency of monitoring and overt rewarding over time, helping the child become more independent.

We conducted the first meta-analysis of organizational skills interventions, which included 12 randomized controlled trials (RCT) and 1054 children (576 treatment, 478 control). The results show that the weighted mean effect sizes for teacher-rated organizational skills are moderate and large for parent-rated organizational skills [34]. We also found that organizational skills training had a small to moderate effect on teacher- and parent-rated symptoms of inattention. Additionally, we found small to medium effect sizes in academic performance as rated by teachers [34]. Findings from two previous qualitative reviews also support these results [17, 35].

Organizational skills training is still a developing research area with several unanswered questions. The body of evidence indicates that executive function interventions are working especially well in younger children [36]. Because children in Denmark start school at age 6, we consider inclusion of this age group important. Thus, we are targeting children 6 years of age and older to expand the knowledge on the effects of OST in younger age groups. Additionally, a number of studies have found that inattention as measured by rating scales improved following OST treatment [34]. This trial will investigate if possible improvements in parent-ratings of attention and organizational skills after OST are also paralleled by changes on neurocognitive tests, which has not been addressed in prior studies. Furthermore, neurocognitive tests will also be used to investigate treatment response as it is unclear if OST works better for some individuals than others. Finally, to the best of our knowledge, this is the first randomized and controlled trial of an organizational skills intervention in a European context (specifically in Denmark). It is important to investigate OST in other contexts outside North America, as school systems and requirements vary across countries. The trial will compare OST treatment to treatment-as-usual (TAU) in children with ADHD referred to clinical services. TAU is chosen as the comparator as children with ADHD who are already in treatment are the target of the intervention. We would like to investigate if OST can provide additional benefits for those children

## Methods

### Objectives

The primary objective of this parallel group, superiority trial is to investigate whether organizational skills training has a positive effect on parent-rated organizational skills in 6–13 year old children with ADHD. The secondary objective is to investigate possible effects on teacher-rated organizational skills, parent-rated inattention, objectively measured sustained attention, and family and school functioning. All these measures will be also investigated at baseline, after the intervention, and at a 6 month follow-up. Additionally, we will investigate predictors of treatment response.

### Trial sites

Participants are recruited at two sites in Southern Denmark: Child Psychiatric Department (CPD) Aabenraa and CPD Vejle.

### Consent to participate

The patients’ treatment-as-usual will not be affected by their participation in this trial. Participants are not prohibited to participate in other treatments. The enrolled families can leave the trial without further explanation at any time. Study investigators can exit a subject from the study if subjects require a higher level of psychiatric care (e.g., inpatient hospitalization). To promote participant retention, trial participants will receive three gift cards worth a total of DKK 400. If participants decide to leave the trial earlier, they will receive gift cards for attended assessments. Transportation costs will be reimbursed for all meetings.

In the intervention group families have the option to use vTime, an online timer app. Access to vTime (http://vtime.dk/) is provided free of charge by the company. vTime has no involvement in the trial design, funding, or any other aspect apart from providing access to the online service.

Non-serious adverse events and serious adverse events will be monitored during intervention and at all endpoint assessments and reported to the ethical committee annually. At all assessments, participants are asked about adverse events by the psychologist conducting the outcome assessments. All adverse event logs are reviewed by the principal investigator. The principal investigator will report severe and serious adverse events to the institutional review board. There are no trial steering committees or data monitoring committees involved as this is not required in trials testing low-risk behavioral interventions [37, 38]. Also, external auditing is only required in pharmaceutical trials according to Danish law. We perform internal reviews that are independent from the sponsors on a regular basis, where we check that all the protocol procedures are followed at both sites and data is stored appropriately.

A child can only participate in the trial if the written consent of all legal guardians (referred to as parents throughout the text) is obtained. Danish law requires written consent by the child above the age of 15 years, and as the children in our trial are younger, we do not collect it. All participating children gave assent for participation. Patients will continue their general assessment and treatment procedure. The treating clinicians make the first approach to the family and provide recruitment and information letters to eligible families. If parents choose to contact the project staff, they will be offered an individual information meeting by a clinical psychologist associated with the trial where the trial will be described and discussed in detail. Parents can choose to take an accompanying person to the information meeting for support. After the meeting, families can decide whether to participate in the trial by providing informed consent. Informed consent is collected by a psychologist, who is a trial research assistant.

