### Inclusion criteria

The following criteria are required for inclusion: ADHD diagnosis according to K-SADS, age between 6 and 13 years (both inclusive), IQ above 80, and written informed consent. Additionally at least one standard deviation (SD) above the mean on the Plan/Organize subscale on the BRIEF verifying problems with organizational skills is required. Both children with and without pharmacological treatment are included in the trial, although we expect the majority of children to receive pharmacological treatment. Children are required to be on stable pharmacological treatment for at least 6 weeks before participation in the trial. Families are recommended not to change the child’s ADHD medication or initiate new medications during the trial period of 10 weeks; however, the final decision about medication is made by the parents and the treating specialist, who is unrelated to the trial. The study researcher team will inquire about possible changes in medication at assessment visits and all changes will be summarized and reported in the results paper.

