### Randomization

Every participant is assigned a participant number. Participants are randomized 1:1 to intervention or control treatment and stratified by trial site (“Aabenraa,” “Vejle”) and age (older/younger). The allocation sequence is computer-generated with a varying block size for which the investigators are blinded. Randomization is performed by a statistician unrelated to the trial. The research assistant (RA) who is carrying out allocation will have no access to allocation sequence. When the subject is ready to be randomized, the RA will send this subject’s ID (and information relevant to stratification) to the statistician. The statistician will enter the ID number in the web-based randomization algorithms and will inform the RA to which study condition the subject is allocated to. The RA will then inform the families about the allocation and enroll them in the trial.

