### Blinding

As the current trial compares an intervention to TAU, it is not possible to blind the participants and their parents. Blinding will be employed in all other possible areas (e.g., administration of the cognitive tasks is carried out by blinded research assistants, randomization, and data analysis) (Fig. 2).

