#### Data storage

All participant information is collected electronically at baseline and endpoints. Our questionnaires are located in the REDCap database, which is a secure web application compliant with the General Data Protection Regulation (GDPR) where questionnaire data is automatically stored. The REDcap has a log of data entry and verification. All data is collected using a participant number and is pseudo anonymized. Only study investigators and statisticians will have access to the final data set.

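### The investigator exit rule takes a child out of the whole study without separating the end of treatment from the end of outcome collection, so the primary outcome can be lost for children who deteriorate after randomisation

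*Protocol article*

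**What the plan says.** The Consent to participate section of the protocol article describes two ways out of the trial.

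- **By the family:** "The enrolled families can leave the trial without further explanation at any time". On payment it adds: "If participants decide to leave the trial earlier, they will receive gift cards for attended assessments".
- **By the investigators:** "Study investigators can exit a subject from the study if subjects require a higher level of psychiatric care (e.g., inpatient hospitalization".

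Neither sentence says what happens to later assessments. The Exclusion criteria already keep out children with serious psychopathology at entry, so the investigator rule works mainly after randomisation.

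Three other sections bear on the point:

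- **Data storage:** "All participant information is collected electronically at baseline and endpoints", with the questionnaires held in REDCap.
- **Analytical model:** a mixed linear regression of change from baseline to post-intervention, adjusted for the baseline value. Multiple imputation applies only when missing-data patterns are unbalanced between the arms. A per-protocol analysis is named as exploratory.
- **Sample size:** a COSS difference of 0.30 with SD 0.36, and an allowance of 10% for dropout.

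**The concern.** A need for a higher level of psychiatric care is a prognostic event that arises after allocation. A rule that lets staff take the child out of the study on that ground, and not only out of the group sessions, ties the loss of the 10-week COSS to how the child is doing. Children who do badly are then the ones most likely to have no primary outcome.

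The planned analysis offers limited protection:

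- With baseline as a covariate, a child who has no COSS after randomisation adds essentially nothing to the estimated treatment effect.
- Imputation is triggered by imbalance between arms. Exits that are similar in number but informative would not trigger it.
- If it is triggered, standard multiple imputation relies on observed data to explain the missingness. For a child exited before week 10, the later worsening is not in the observed COSS data.

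The arms could also differ in how often worsening is noticed. The Abstract says adverse events are monitored at weekly therapy sessions as well as at assessments, and only OST children have those sessions during the intervention period. The documents do not show that exits differ by arm for this reason, but they leave room for it.

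**Working it through.** **1. The plan's own figures.** Two-sample t-test, 5% two-sided (sidedness is assumed; the article does not state it).

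- Primary: effect 0.30 / 0.36 = 0.833 SD. Required n is 31.25, so 32 per group; power at 32 is 0.907. This matches the stated 32 at 90%.
- Secondary: effect 0.5 SD. Required n is 63.8, so 64 per group; power at 64 is 0.801. This matches the stated 64 at 80%.
- Dropout: 64 × 1.10 = 70.4, so 71 as stated. Dividing instead, 64 / 0.90 = 71.1 gives 72. The difference of one child per arm is immaterial, since 71 × 0.90 = 63.9.

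**2. Is precision at risk?** Starting from 71 per arm:

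| Total loss | Remaining per arm | Power, primary | Power, secondary |
|---|---|---|---|
| 10% | 63.9 | 0.997 | 0.801 |
| 20% | 56.8 | 0.993 | 0.752 |
| 30% | 49.7 | 0.984 | 0.694 |

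The primary comparison keeps ample power even under heavy loss. The issue is bias.

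**3. Size of the bias.** Let *f* be the share of an arm that is exited and *k* the number of SDs by which exited children would score worse than those retained. The full-arm mean is worse than the completers' mean by *f* × *k* × SD. The bias in the completers' difference is therefore

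(*f*_OST × *k*_OST − *f*_TAU × *k*_TAU) × SD.

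A positive value flatters OST; a negative value works against it. With the same *k* in both arms this becomes (difference in exit rate) × *k* × 0.36. The documents give neither *f* nor *k*, so the rows below are assumptions.

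| Arm difference in exits | *k* | Bias, COSS points | Share of 0.30 |
|---|---|---|---|
| 0 points | any | 0 | 0% |
| 2 points | 1 | 0.02 × 0.36 = 0.007 | 2.4% |
| 5 points | 1 | 0.05 × 0.36 = 0.018 | 6% |
| 10 points | 1 | 0.10 × 0.36 = 0.036 | 12% |
| 10 points | 1.5 | 0.10 × 1.5 × 0.36 = 0.054 | 18% |

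Five per cent of 71 is 3.55, so the third row means three to four more children exited in one arm than in the other.

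**4. Equal counts are not enough.** Suppose 5% exit in each arm, with *k* = 1.5 in OST and 0.5 in TAU. The bias is (0.05 × 1.5 − 0.05 × 0.5) × 0.36 = 0.018 points, although the exit rates are identical. The bias vanishes only when exits match in both rate and type.

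**The case against.** The strongest reply is that the rule is permissive and says less than the concern needs. It does not say that collected data are discarded, that questionnaires stop, or that the child leaves the analysis. The gift-card sentence concerns families who choose to leave, not investigator exits. Calling the per-protocol analysis exploratory suggests that the main analysis is not per-protocol. The article condenses a full protocol that is not shown, and analysis-set definitions belong there or in the SAP. Exits on this ground may be few, given the exclusion of serious psychopathology at entry; the same rule covers both arms; and the illustrated bias is small.

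Most of this stands as a limit on the claim. The absence of an analysis-set definition is not part of the point. What remains is the rule as printed: its object is the study, its trigger is deterioration, and it makes no provision for continued outcome collection.

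A reader might draw three stronger conclusions that the documents do not support.

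- **That outcomes are in fact lost selectively.** No exit rate, by arm or overall, is given. Selective loss is a possibility, not something shown.
- **That unblinded staff decide on exits.** The registration table lists the investigator as blinded. The principal investigator's therapist training and weekly adherence meetings (Treatment fidelity) give grounds for doubt, but they do not settle who decides or what that person knows.
- **That enrolment after disclosure breaks the randomised comparison.** The Randomization section does say "The RA will then inform the families about the allocation and enroll them in the trial", and under Blinding "it is not possible to blind the participants and their parents". But Consent to participate says "After the meeting, families can decide whether to participate in the trial by providing informed consent", and the Inclusion criteria require "age between 6 and 13 years (both inclusive), IQ above 80, and written informed consent". A child's ID goes to the statistician only once the child is ready for randomisation. Consent and eligibility therefore appear to come first, and enrolment is most naturally an administrative step. Nothing says that a family declining after allocation is dropped or replaced.

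**Conclusion.** The point holds in limited form. The exit rule does not distinguish stopping the intervention from stopping outcome collection. Applied as written, it can remove the primary outcome of children who deteriorate after randomisation. That loss can be informative, and the conditional imputation rule would not reliably correct it.

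The likely size is modest: about 0.018 COSS points, or 6% of the 0.30 target, for a 5-point arm difference in exits with exited children 1 SD worse. It is about zero when exits are equal in rate and type, and 0.054 points (18%) in the most extreme case shown. Every one of these figures rests on assumed exit rates and severity. The sample size and the power for the primary outcome are not in question. The change is worth making because it costs little and removes an avoidable source of bias.

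**What to change.** Leave the clinical decision as it is and separate data collection from it. Add to Consent to participate, in substance:

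> A child exited because a higher level of psychiatric care is needed stays in outcome follow-up. The 10-week and 6-month COSS and the other REDCap questionnaires are still requested unless the parents withdraw consent. The child is kept in the primary analysis in the arm as randomised.

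**Cost.** One change of protocol wording. The questionnaires are already collected electronically, so requesting them needs no extra staff or visits. Families of these children carry a small added burden at a difficult time, and the right to withdraw consent stays intact. The gain is partial: the CANTAB tests, including the secondary sustained-attention outcome, are administered by research assistants and may still be missing for these children.
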